# 4.5 Withdrawal of individual subjects

#

# 4.5.1 Specific criteria for withdrawal

Employees are able to withdraw at any time without reason.

#

# 4.6 Replacement of individual subjects after withdrawal

None

# 4.7 Follow-up of subjects withdrawn from treatment

Statistical analyses will be performed, based on the intention-to-treat principle. Subjects will remain in the analyses according to the allocated intervention or control group, after randomisation. Per-protocol analyses will be performed on all participants in the control group, and the participants in the GMI group, who have attended at least 70% of the GMI-sessions.

#

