# 3.3 Design

In this study, a randomized controlled trial design will be employed, with pre-stratification on environmental modifications. That is, two strata will be created, with (6 wings) and without (7 wings) environmental modifications. Within each stratum, wings will be randomly assigned to GMI or no GMI. Randomisation will take place at wing level. We decided to apply cluster randomisation on wing level to avoid contamination with employees in the control group. Consequently, the study will consist of four research arms, i.e. (1) both GMI and the environmental modifications, (2) environmental modifications/no GMI, (3) GMI/no environmental modifications, (4) no GMI/no environmental modifications (control group). The design of the VIP project is shown in appendix 1.

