# 4.2 Secondary outcome measures

Daily physical activity will be assessed by the Short Questionnaire to Assess Health Enhancing Physical Activity (SQUASH) (69). This questionnaire assesses the duration, frequency, intensity of active home-to-work transport, physical activity at work, sedentary time at work and home, activity in leisure time and household activities, and sport. The SQUASH is a fairly reliable (r=0.58) and reasonably valid (r=0.45) questionnaire. Its validity and reliability are comparable to other physical activity questionnaires (70).

Physical activity and sedentary behaviour will also be measured objectively in a random sample of 100 participants, consisting of the GMI group (n=25), the GMI and environmental modifications group (n=25), the environmental modifications only group (n=25) and the control group (n=25). This subsample will be asked to wear the accelerometer during a period of 7 days, both at baseline, 6 and 12 months follow-up. On all days of the week, participants fill out a short questionnaire (diary) on the exact wearing times of the Actigraph (i.e. the time at which the Actigraph was put on and off) and the times of leaving and arrival at home and work (to determine the exact wearing time at work and leisure time). At the end of each week, they will be asked to hand it back to the researcher/research assistant on appointment.

Detachment and relaxation will be assessed by the recovery experience questionnaire, which is developed by Sonnentag et al. (71) and showed satisfactory reliability (r=0.84) and reasonable validity (r=0.46). A Dutch version of this questionnaire showed high reliability (r=0.92) in a pilot study by Bloom et al. (72). We will adapt this scale to a work context, starting each item with “During a break at work…”, instead of “During time after work…” as written in the original questionnaire of Sonnentag et al. (71). This detachment and relaxation questionnaire consist of 8 items and is derived from the recovery experience scale (71). It consists of items such as “I forget about work”, “I don’t think about work at all”, “I kick back and relax” and “I do relaxing things”. Each item can be scored on a 7-point scale, ranging from “never” to “always”. Both the original and modified version of the recovery experience scale (71) will be assessed.

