# 6. Statistical analysis

First of all, baseline characteristics will be analyzed on differences between the four intervention arms, by two-way analysis of variance for numerical data and chi-square and logistic regression for categorical data. Multilevel regression analyses will be performed regarding the effectiveness of the intervention on need for recovery, the secondary outcome measures physical activity/relaxation and other work and health-related variables after 6 months (short-term) and 12 months (long-term). The intervention effect will be estimated in each stratum and a pooled estimated effect is calculated across strata. Multilevel analysis takes into account the clustering of observations of employees within the same wing. All analyses will be performed crude, and adjusted for possible confounders, such as gender and age. Also, these variables will be checked for effect modification. Correction for baseline values will be applied. Analyses will be carried out to test differences in sick leave between the four study intervention arms. All statistical analyses will be performed according to the intention-to-treat principle. Per protocol analyses will be performed to investigate the effects of the intervention in participants who showed high compliance (>70%) to the GMI intervention. Where necessary, missing data will be imputed using multiple imputation techniques. For all analyses a two tailed significance level of p<0.05 is considered statistically significant. All analyses will be performed with SPSS 19.0 (SPSS Inc. Chicago, Illinois, USA).

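### The per-protocol set leaves out arm 2 and does not define the GMI group, so the analysis either loses its same-stratum comparator or drops the modified stratum

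*Protocol*

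**What the plan says.** The arms are: 1, GMI plus environmental modifications; 2, modifications only; 3, GMI only; 4, neither.

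- **Per-protocol set (Protocol, Section 4.7).** "Per-protocol analyses will be performed on all participants in the control group, and the participants in the GMI group", the latter limited to those "who have attended at least 70% of the GMI-sessions". Section 4.7 does not say which arms make up the GMI group.
- **Per-protocol aim (Section 6).** "Per protocol analyses will be performed to investigate the effects of the intervention in participants who showed high compliance (>70%) to the GMI intervention". No comparator is named.
- **Control group (Section 3.3).** The label is attached to one arm: "4) no GMI/no environmental modifications (control group").
- **GMI group (Section 4.2).** The accelerometer subsample is listed as "the GMI group (n=25), the GMI and environmental modifications group (n=25), the environmental modifications only group (n=25) and the control group (n=25"). Here the GMI group is arm 3, separate from the combined arm, and the modifications-only arm is separate from the control group.
- **What is randomised (Section 3.3).** "Within each stratum, wings will be randomly assigned to GMI or no GMI".
- **Planned estimate (Section 6).** "The intervention effect will be estimated in each stratum and a pooled estimated effect is calculated across strata".

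**The concern.** Only GMI is randomised, and only within an environmental stratum. The randomised comparator for arm 1 is therefore arm 2, and for arm 3 it is arm 4. A per-protocol set made of arm 4 plus GMI attenders has no arm 2. Anyone building the data set from Section 4.7 must then decide what the GMI group is, and neither choice yields the analysis that Section 6 describes. One choice invites a comparison across strata that were not randomised. The other silently restricts the analysis to one stratum.

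The result is likely to be read as the effect of GMI when employees take it up. If it differs from the intention-to-treat result, the reader could not tell whether attendance, the work environment, department differences or the missing stratum explains the gap.

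**Working it through.** The protocol gives no size, power or attendance rate for the per-protocol set, so there is no stated figure to reproduce. The inputs are the wing and employee counts of Appendix 1 (arm 1: 3 wings, arm 2: 3, arm 3: 4, arm 4: 3; 101 planned employees in each). They agree with the totals: 3 + 3 + 4 + 3 = 13 wings and 4 × 101 = 404 employees. The yardstick is the 12-point relevant difference in Section 3.5.

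**1. Is arm 2 in the set?** The Summary and Section 3.3 label arm 4 the control group. Section 4.2 lists the modifications-only arm beside the control group. Section 4.4 says the control group gets no specific intervention, which cannot describe arm 2. Section 6.1 sets three intervention arms against the control group. On this usage arm 2 is out. That removes 3 of 3 + 3 = 6 no-GMI wings and 101 of 404 employees (25%).

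**2. If the GMI group is arms 1 and 3.** The modified stratum then contains GMI attenders and no comparator, so the stratum-specific estimate does not exist there and there is nothing to pool. What can still be computed is attenders of both arms against arm 4. Let *w* be the share of attenders who come from arm 1, and *D* the difference in mean need for recovery between modified and unmodified wings without GMI, as left after adjustment. With the same GMI effect in both strata:

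pooled contrast = *w* × (GMI effect + *D*) + (1 − *w*) × GMI effect = GMI effect + *w* × *D*

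By wings *w* = 3/7 = 0.43. By planned employees with equal attendance *w* = 101/202 = 0.50. The protocol gives no value for *D*; the following values are assumed.

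| Assumed *D* (points) | *w* = 0.43 | *w* = 0.50 |
|---|---|---|
| 3 | 1.3 | 1.5 |
| 6 | 2.6 | 3.0 |
| 12 | 5.1 | 6.0 |

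If attendance were 90% in one GMI arm and 50% in the other (also assumed), *w* would lie between 50/(50 + 90) = 0.36 and 90/(90 + 50) = 0.64, and the carried amount between 1.1 points (*D* = 3) and 7.7 points (*D* = 12). *D* is not only the effect of the modifications. They go to two departments (Section 4.4.2) and the protocol describes no randomisation of them, so *D* also holds existing department differences.

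**3. If the GMI group is arm 3 only.** The contrast is arm 3 attenders against arm 4, both without modifications, so the carried amount is 0. The modified stratum is lost: 6 of 13 wings and 202 of 404 planned employees (50%). Section 6 does not restrict the per-protocol analysis to one stratum.

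**4. Selection, under both readings.** Let *p* be the attendance rate and *d* the attender minus non-attender difference in the outcome that is not due to GMI. Controls contain both kinds of people, so the bias is *d* − *p* × *d* = (1 − *p*) × *d*. With assumed *p* = 0.70 and *d* of size 3, 6 or 12 points it is 0.9, 1.8 or 3.6 points before adjustment. The sign of *d* is unknown.

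**5. The two thresholds.** Section 4.7 says at least 70%; Section 6 has "to investigate the effects of the intervention in participants who showed high compliance (>70%) to the GMI intervention". With three sessions, 2/3 = 67% fails both and 3/3 passes both. With the booster counted, 2/4 = 50% fails both and 3/4 = 75% passes both. The two wordings select the same people.

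**The case against.** A reader might infer that the per-protocol GMI effect is necessarily mixed with the environmental effect. The protocol does not support that. Mixing needs a narrow control group (arm 4) and a broad GMI group (arms 1 and 3) in the same sentence, and also an analysis that ignores strata. On the usage of Section 4.2 both terms are narrow and the mixing is zero. If the stratified rule of Section 6 is followed, the contrast for arm 1 cannot be formed at all, which is a different failure from a biased one. This part of the objection stands.

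A broad reading of both terms is also possible. The preceding sentence in Section 4.7 contrasts the allocated intervention with the control group after randomisation, and only GMI is randomised. Section 3.3 also mentions the control group when it explains why wings are randomised. Arm 2 would then belong to the control group, and the comparisons would be arm 1 with 2 and arm 3 with 4. This may be what was meant, but it rests on loose usage against the explicit labels in the Summary and Sections 3.3, 4.2 and 4.4.

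A reader might also infer that selection flatters GMI. Nothing shows that: employees with high need for recovery may attend more, which would reverse the sign. Section 6 already plans baseline correction and confounder adjustment, so the figures in step 4 overstate the bias to the extent that baseline variables explain *d*. Residual selection is a general limit of attendance-based analyses.

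Finally, the per-protocol analysis is supplementary to intention-to-treat. That limits the consequence. It does not make this a matter to be left to a later analysis plan, because Section 4.7 already fixes the set.

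**Conclusion.** The point holds as a defect in the definition of the per-protocol set. Arm 2 is left out on the protocol's own label for the control group, and the GMI group is undefined.

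If arms 1 and 3 are meant, the stratum-specific and pooled effects cannot be formed, and a pooled comparison with arm 4 carries roughly 43 to 50% of the difference between non-randomised strata. That is 1.3 to 6.0 points for assumed differences of 3 to 12 points, against a relevant difference of 12. The upper end assumes a stratum difference as large as the full relevant difference. If arm 3 alone is meant, there is no mixing, but half of the planned participants leave the analysis.

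Selection bias of unknown size and direction can remain either way. The point sizes rest on assumed stratum differences, attendance and attender differences; the shares and counts come from Appendix 1. The primary result is not at risk, and the differing threshold wording is of no consequence.

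**What to change.** In Sections 4.7 and 6, state that:

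- GMI attenders in arms 1 and 3 are compared with all no-GMI participants of the same environmental stratum (arm 1 with arm 2, arm 3 with arm 4);
- the baseline and confounder adjustment already planned is applied, and the stratum estimates are pooled as in the main analysis;
- the result is reported as a non-randomised, supplementary comparison.

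This takes two or three sentences, needs no new data, and restores arm 2 to the set. It removes the cross-stratum comparison and the loss of a stratum; it does not remove selection on attendance, hence the label.

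A complier-average analysis with randomised GMI as instrument and wing-clustered standard errors could be added, but only as an option. It is less precise. It also assumes that allocation does nothing for low attenders, which is doubtful here: the social media platform is open to everyone allocated to GMI (Section 4.4.1), and partial attendance may have some effect.

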# 4.8 Premature termination of the study

As this trial is non-medical, but stimulates healthy behaviour instead, the study is not likely to be terminated prematurely.

#

# 5. Safety reporting

# 5.1 Section 10 WMO event

This is not an investigational medicinal study

# 5.2 Adverse and serious adverse events

This is not an investigational medicinal study.

#

# 5.3 Follow-up of adverse events

No serious adverse events from the questionnaires and the VIP program are expected. For this reason, no follow-up of adverse events will be performed. The VIP program consists of GMI-sessions, supported by a social media platform, and environmental modifications at the worksite. If employees encounter problems (mentally or physically) at any moment during the VIP program, teamleaders and/or the principal researcher will refer them to the occupational physician or the company’s social worker, who is physically present on the premises of the organisation.

# 5.4 Data Safety Monitoring Board (DSMB)

Not applicable.

# 6. Statistical analysis

First of all, baseline characteristics will be analyzed on differences between the four intervention arms, by two-way analysis of variance for numerical data and chi-square and logistic regression for categorical data. Multilevel regression analyses will be performed regarding the effectiveness of the intervention on need for recovery, the secondary outcome measures physical activity/relaxation and other work and health-related variables after 6 months (short-term) and 12 months (long-term). The intervention effect will be estimated in each stratum and a pooled estimated effect is calculated across strata. Multilevel analysis takes into account the clustering of observations of employees within the same wing. All analyses will be performed crude, and adjusted for possible confounders, such as gender and age. Also, these variables will be checked for effect modification. Correction for baseline values will be applied. Analyses will be carried out to test differences in sick leave between the four study intervention arms. All statistical analyses will be performed according to the intention-to-treat principle. Per protocol analyses will be performed to investigate the effects of the intervention in participants who showed high compliance (>70%) to the GMI intervention. Where necessary, missing data will be imputed using multiple imputation techniques. For all analyses a two tailed significance level of p<0.05 is considered statistically significant. All analyses will be performed with SPSS 19.0 (SPSS Inc. Chicago, Illinois, USA).

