3.5 Sample size calculation The sample size calculation is based on the main outcome measure, i.e. need for recovery, measured by the need for recovery questionnaire (63). The mean need for recovery score is 27,30 (SD=29,75) according to the validation study of Van Veldhoven et al. (63). Minimal relevant difference on the need for recovery scale, with a range from 0 to 100, was set on 12. This was based on the articles by de Croon et al. (64) and Kuijer et al. (65), in which on average a relevant difference of 12 was found in nurses, truck drivers and refuse collectors, after an intervention, such as change in work hours (64) or job rotation (65). Using a power of 0.9, in total 260 employees are needed. Because randomisation takes place at wing level, a cluster correction was applied. An intraclass correlation (ICC) of about 0.025 is assumed, based on previous studies showing that worksite level ICC’s for health-related outcomes are generally small (66-68). This leads to a cluster correction factor of 1 + (13-1)* 0.025 = 1.3. Based on this cluster correction, a total of 1.3*260 = 338 employees will be needed. Furthermore, by applying a correction for repeated measurement we will win some precision, therefore an additional correction by a factor 0.9 seems justified, resulting in 0.9×338=305 employees in total. Finally, accounting for a loss to follow-up of 25% in twelve months, a total of 404 employees for the four intervention arms will be needed at baseline. Based on the source population of 980 employees (13 wings), the number of 404 employees is reached at a participation rate of 42 percent. This percentage is considered feasible, because all teamleaders and their employees within a wing will be asked to participate.

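### Section 6 tests baseline differences without regard to wings: if the protocol's ICC of 0.025 applies, a nominal 5% test of the randomised GMI contrast has a true size of about 14%

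*Protocol*

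**What the plan says.** The first analysis named in section 6 of the protocol concerns baseline comparability: "baseline characteristics will be analyzed on differences between the four intervention arms, by two-way analysis of variance for numerical data". Variables that are not numerical get a separate pair of methods in the same sentence, chi-square tests and logistic regression. No wing term is mentioned for any of these three methods.

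Clustering appears in section 6 only with the multilevel regression models, which are assigned to the effectiveness outcomes: "Multilevel analysis takes into account the clustering of observations of employees within the same wing". The significance rule is general: "For all analyses a two tailed significance level of p<0.05 is considered statistically significant".

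On the design, section 3.3 says "Randomisation will take place at wing level", and that "two strata will be created, with (6 wings) and without (7 wings) environmental modifications". GMI is then allocated at random to wings within each stratum. Section 3.5 acknowledges dependence within wings: "An intraclass correlation (ICC) of about 0.025 is assumed".

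**The concern.** Two-way ANOVA, the ordinary chi-square test and ordinary logistic regression all compute their standard errors as if each employee were an independent observation. When whole wings are allocated and employees within a wing resemble each other, those standard errors are too small and the p-values too low. The protocol allows for this in its sample size and its effectiveness models, but not in its first analysis.

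The effect is clearest for GMI. Under section 3.4, consent and baseline measurement come before the GMI randomisation, which an independent researcher carries out. Any baseline difference between GMI and non-GMI wings within a stratum is therefore chance, and a valid 5% test should flag it 5% of the time. The test as described would flag it more often. What is at stake is the accuracy of what is reported about baseline comparability: a table with too many significant differences could make a sound randomisation look faulty.

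**Working it through.** **Inputs**
- Baseline sample: 404 employees in 13 wings (section 3.5); wings split 3, 3, 4 and 3 over the arms, 101 employees per arm (Appendix 1).
- ICC: 0.025, assumed in section 3.5 from health-related outcomes in worksite studies.
- Significance level: 5%, two-sided (section 6).

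**The plan's own figures.** The protocol states no error rate for the baseline tests, so only the sample size can be reproduced. A difference of 12, SD 29.75, two-sided 5% and power 0.9 give 130 per group, 260 in total, as stated. Then 260 × 1.3 = 338, and 338 × 0.9 = 304.2, stated as 305. Finally 305/0.75 = 407, against 404 stated, which is within rounding tolerance. The 404 is used below.

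**Design effect.** Average wing size m = 404/13 = 31.1.

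DE = 1 + (m − 1) × ICC = 1 + 30.1 × 0.025 = 1.75.

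The protocol's own factor, 1 + (13 − 1) × 0.025 = 1.3, puts the number of wings where the number of participants per wing belongs, so it is not used here.

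**True size of a nominal 5% test that ignores wings**
- 1 df (GMI main effect; likewise each other term of the two-way ANOVA): 2 × [1 − Φ(1.96/√DE)] = 2 × [1 − Φ(1.96/1.324)] = 2 × [1 − Φ(1.481)] = 13.9%, or 13.9/5 = 2.8 times nominal.
- 3 df (four-arm comparison, with no true difference between any arms): P(χ²₃ > 7.815/1.75) = 21.6%, or 4.3 times nominal.

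**Range over the ICC, m = 31.1**

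| Assumed ICC | DE | 1 df (GMI) | 3 df (four arms, no true difference) |
| --- | --- | --- | --- |
| 0.005 | 1.15 | 6.8% | 7.9% |
| 0.01 | 1.30 | 8.6% | 11.1% |
| 0.025 | 1.75 | 13.9% | 21.6% |
| 0.05 | 2.50 | 21.6% | 37.3% |

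The values other than 0.025 are assumptions, to show sensitivity.

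**Simulation check** (20,000 runs, wings 3/3/4/3, 101 employees per arm, wing random effect, no true difference). At ICC 0.025 the GMI term rejected in 14.0% of runs, the four-arm F test in 21.8%, and a four-arm chi-square test on a binary variable with prevalence 0.5 in 21.7%. At ICC 0.01 and 0.05 the GMI term rejected in 8.9% and 22.1%. At ICC 0 all rates were 4.9% to 5.0%, so the excess comes from clustering alone.

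**The case against.** The strongest reply is that this is descriptive work with no consequence for the trial's conclusions. The effectiveness models include wings, correct for baseline values, and are run both crude and adjusted. No treatment estimate, confidence interval or efficacy p-value changes. That stands, and it is why the point is minor.

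Three stronger readings are tempting, and the documents do not support them.

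- *A reader might infer that false imbalances occur three to four times too often in general.* The factor above four belongs to the 3-df comparison of all arms, which includes the environmental contrast. Section 4.4.2 places the modifications in two departments, and the protocol describes no random choice of them. A baseline difference between strata may be real, so it cannot simply be called false. For the randomised contrast the factor is 2.8. It also depends on an ICC that section 3.5 assumes for health-related outcomes; none is given for age, sex or education, and theirs could be lower or higher.
- *A reader might infer that baseline p-values will choose the covariates,* because the adjustment is for "adjusted for possible confounders, such as gender and age". Section 6 contains no such rule. The open wording is detail that a statistical analysis plan may close, and is not an error here.
- *A reader might infer that baseline testing has no use at all in this trial.* Since the strata are not described as randomised, comparing them at baseline is informative. The fault there is the method, because the standard errors are too small for that contrast as well.

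What remains is that the named methods do not match the unit of allocation.

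**Conclusion.** The point holds in a narrow form. The baseline tests in section 6, as described, ignore the wings that are randomised and would give p-values that are too small. If the protocol's ICC of 0.025 applies to the baseline variables and wings average about 31 participants, the nominal 5% test of the GMI contrast has a true size of about 14%. It would be about 9% at ICC 0.01 and 22% at 0.05. The four-arm figure of about 22% at ICC 0.025 is conditional on there being no real difference between the environmental strata, which the design does not guarantee.

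The effectiveness analysis is not affected, and no decision stated in the protocol rests on these tests. The correction is worth making because it is nearly free and brings the baseline analysis into line with the protocol's own treatment of clustering.

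**What to change.** In section 6, replace the baseline significance tests with a descriptive table by arm: means and SDs for numerical variables, proportions for categorical ones, and the number of wings and participants in each arm. If the environmental strata, which are not described as randomised, are to be compared at baseline, do so with the multilevel approach already planned for the outcomes, with wing as a random effect.

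The cost is about two sentences of protocol text. No further data are needed, and the analysis work falls slightly. The only thing given up is a column of p-values for the randomised contrast, where any difference is chance by design; the informative comparison between strata is kept, with standard errors that reflect the 13 wings.
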